## Abstract

**Background:** In Pakistan, stillbirth rates and early neonatal mortality rates are amongst the highest in the world. The aim of this study is to provide proof of concept for using a computational model of fetal haemodynamics, combined with machine learning. This model will be based on Doppler patterns of the fetal cardiovascular, cerebral and placental flows with the goal to identify those fetuses at increased risk of adverse perinatal outcomes such as stillbirth, perinatal mortality and other neonatal morbidities.

**Methods:** This will be prospective one group cohort study which will be conducted in Ibrahim Hyderi, a peri-urban settlement in south east of Karachi. The eligibility criteria include pregnant women between 22-34 weeks who reside in the study area. Once enrolled, in addition to the performing fetal ultrasound to obtain Dopplers, data on socio-demographic, maternal anthropometry, haemoglobin and cardiotocography will be obtained on the pregnant women.

**Discussion:** The machine learning approach for predicting adverse perinatal outcomes obtained from the current study will be validated in a larger population at the next stage. The data will allow for early interventions to improve perinatal outcomes.

## Introduction

A pregnant woman and her newborn are most vulnerable around the time of delivery and the postnatal period
^1^. Stillbirths and early neonatal deaths within 7 days of life are a major cause of perinatal mortality. In 2013, 2.8 million neonatal deaths
^2^ and an equal number of stillbirths occurred globally
^3^. The majority of all stillbirths and neonatal deaths occur in low-income and middle-income countries in south Asia and sub-Saharan Africa
^3^. Pakistan is one of the countries where the stillbirth rate (43/1000 total births) and neonatal mortality rate (55/1000 live births) are among the highest in the world
^4^. The figures for perinatal mortality remained unchanged between Pakistan Demographic and Health Survey (PDHS) 1990–91 and PDHS 2012–13
^4^. These numbers highlight the importance of evaluating new techniques to identify high-risk pregnant women who can then subsequently receive personalized care to improve perinatal outcomes.

The ductus venosus, ductus arteriosus and foramen ovale, are essential shunts in the fetal circulation which play an important role in development of the fetal heart and circulation during the second and third trimester
^5^. The ductus arteriosus is a wide vessel connecting the pulmonary arterial trunk to the descending aorta with approximately 40% of the cardiac output directed through it
^6^. The ductus venosus connects the umbilical vein to the inferior vena cava at its inlet to the heart
^5^. This vessel plays a critical role in the fetal circulation because it shunts oxygenated and nutrient-rich venous blood to the brain and myocardium instead of the fetal liver
^7^. The Doppler examination of the ductus venosus is used to identify hypoxaemia, cardiac decompensation and placental compromise
^8^ with abnormal waveforms (i.e. absent or reversal of end diastolic flow) being strongly associated with perinatal mortality in fetuses with early-onset IUGR
^9^. The aortic isthmus (AoI) forms a watershed between the upper body (including the brain) and lower body (including the placenta)
^5^. Fetuses with retrograde AoI blood flow fail to shift their right ventricular output from the pulmonary to the systemic circulation, indicating cerebral hypoxia
^10^. However, there is limited knowledge regarding the pattern of redistribution in the fetal cardiovascular systems which lead to these changes
^11^.

Fetal blood flow waveforms assessed via Doppler ultrasound to indicate wellbeing of the fetus have been in practice for nearly four decades
^12^. Abnormal blood flow patterns in the fetal circulation detected by Doppler ultrasound may indicate poor fetal prognosis
^13^. A recent Cochrane review on 19 trials involving approximately 10,000 women reported fewer perinatal deaths (RR-0.71, 95% confidence interval (CI) 0.52 to 0.98), fewer inductions of labour (RR 0.89, 95% CI 0.80 to 0.99) and fewer caesarean sections (RR 0.90, 95% CI 0.84 to 0.97) in women who received Doppler ultrasound to assess fetal well-being
^13^. A recent review of approximately 55,000 women reported that flow velocity waveforms across the uterine artery have a very high specificity (93.3%; 95% CI 90.4-95.5) for identifying growth restricted fetuses
^14^.

Flow changes in several other major arteries of the feto-placental circulation, as detected by Doppler echocardiography, may provide important information regarding fetal compromise which may lead to perinatal morbidity and mortality
^11^. Doppler parameters such as umbilical artery, middle cerebral artery (MCA), aortic isthmus and ductus venosus have been used for identification, risk stratification and further management of high risk pregnancies
^15^. Fetal hypoxia and acidosis may lead to absence, or even reversal, of end diastolic flow in the umbilical artery, which is associated with high perinatal morbidity and mortality
^16^. An increase in end-diastolic flow in the MCA, considered to be a brain sparing physiological phenomenon, has been seen in pregnancies suspected of intrauterine growth restriction
^17^.

Lumped computational models have been proposed to recreate and increase our understanding regarding the regulation of the utero-placental and fetal circulation
^5^. The main advantage of these models is that changes in individual parameters (which may not be possible through
*in vivo* or animal based experiments) and their effect on Doppler indices can be evaluated
^6,
11^. Machine learning models can be used to predict IUGR in the second trimester
^7,
11^. This model showed that IUGR fetuses had aortic isthmus flow changes that depend on cerebral vasodilation and increase in peripheral resistance with the latter being a major determinant, while MCA flow was mainly affected by changes in cerebral resistance
^11^. The results also suggested that patient specific haemodynamic parameters estimated with the computational model had the advantage of studying the effects of individual flow changes across the fetus and placenta which cannot be assessed in a clinical setting
^7^. This would help in understanding the pathophysiology of disease states in a more comprehensive manner and suggest possible interventions.

The Doppler flow allows us to assess the fetus that is at risk irrespective of the gestational age. It will also allow us to identify at-risk fetus without relying on anthropometric measures. As long as we are able to able to obtain the Doppler patterns on the fetus we will be able to determine if the patterns are normal or abnormal, with less of a concern of determining an accurate gestational age. In addition to obtaining fetal Dopplers, one echocardiogram will be performed on the mother. The echocardiogram will look at the four chamber view of the heart in the mother. This data may help us identify maternal etiology for poor perinatal outcomes and thus provides insights into intervention.

Though UmbiFlow (jointly developed by Medical Research Council (MRC) Unit for Perinatal Mortality, the MRC and the Centre for Scientific and Industrial Research (CSIR) South Africa), a portable device used to detect IUGR by assessing continuous wave Doppler blood flow across the placental end of the umbilical artery reported reduced number of unnecessary referrals to a higher level health facility in cases suspected of IUGR
^8^, it studies waveform across one arterial bed while our model takes into account 6 arterial beds which play a critical role in the fetal circulation.

The aim of this study is to obtain proof of concept for using a computational model of fetal hemodynamics, combined with machine learning based on Doppler patterns of the fetal cardiovascular, cerebral and placental flows, to identify those at increased risk of adverse perinatal outcomes such as stillbirth, perinatal mortality, and other neonatal morbidities. We will also compare the sensitivity and specificity of UmbiFlow with the machine learning model in predicting adverse perinatal outcomes.

## Study protocol

Study design, duration and setting – This will be a prospective one group cohort study for a period of twelve months which will be based in Ibrahim Hyderi, a peri-urban settlement of approximately 70,000 on the south east of Karachi. It is one of the seven union councils in Bin Qasim town which has a population of one million. A primary health care clinic (PHC) run by the Department of Peadiatrics and Child Health, The Aga Khan University (AKU) provides free care of early childhood illnesses and pregnancy services including antenatal checkups and free ultrasound. Pregnant women self-refer for basic ultrasound and antenatal follow-ups.

Study subjects and eligibility criteria- Pregnant women between 22–34 weeks who reside in Ibrahim Hyderi Goth. This site was chosen for their static population and the presence of demographic surveillance system setup by the Department of Pediatrics and Child Health, Aga Khan University for several years. The presence of this system ensures that women can be tracked during pregnancy and after delivery to ascertain their outcomes, which is critical to this project. This gestational age is most feasible to perform fetal Doppler that may help predict adverse outcomes. The eligibility criteria of the study are as follows:

Inclusion criteria:

• Pregnant woman coming to the ultrasound clinic between 22–34 weeks of gestation.• Written informed consent obtained• Resident of the study area

Exclusion criteria:

• Multiple gestation• Known congenital anomaly in the fetus or newborn• Refusal for the ultrasound• Poor echocardiographic images for Doppler acquisition

Outcomes –

The primary outcomes of this study include:

• Stillbirth (baby born with no signs of life at or after 28 weeks of gestation) and• Early neonatal mortality (death of a baby within the first 7 days of life).

The secondary outcomes include:

• IUGR – Fetal weight that is below the 10
^th^ centile for gestational age on ultrasound• Prematurity – Birth of a fetus < 37 weeks of gestation• LBW – Birth weight < 2.5 kg• Birth asphyxia – Delayed cry after at least 1 minute of life• Early neonatal sepsis – Any 1 of the following signs: fever > 38 or < 35 Celsius, convulsions, lethargy, poor feeding, chest in drawing and tachypnea (respiratory rate > 60 breaths per minute) within 7 days of life
^9^

Sample size estimation – The sample size is based on outcomes of the pregnancies and not based on etiology of outcome. For the training of the machine learning, as much data as possible is required and this would be typically in the order of magnitude of thousands of patients. Given that this is not feasible in the pilot study, the training data will be mainly synthetically generated through a computational model of the fetal circulation. This allows the generation of thousands of 'individuals'. A recent randomized clinical trial conducted on machine learning in heart failure with 1106 patients with 20% having an adverse primary outcome and 5 different phenotypes, it was seen that above a sample size of 500 patients, the learned information becomes stable and doesn't change much
^10^. Additionally, we will be using socio-demographic, and pregnancy and labor characteristics, along with the Doppler, where the combined analysis should make the detection additionally more robust.

In the study area there are 30 stillbirths per 1000 total births while there are 30 neonatal deaths per 1000 live births. If 500 pregnant women are to be enrolled in the study duration, we expect to find approximately 25–30 adverse perinatal outcomes. To account for loss to follow up, we will inflate the sample size by 5% and enroll 525 pregnant women. Sample size was estimated from experience with the proposed machine learning approach, where stability of the learning phase was reached around 500 included patients
^18^, combined with the fact that data augmentation of the training set will be performed using the previously validated computational model of the fetal circulation
^7^.

Recruitment – Household surveillance will be done by community health workers (CHWs) in the catchment area in a sequential manner to identify pregnant women. Eligible women between 22–34 weeks of gestation on last menstrual period (LMP) will then have the purpose of the study explained to them and be invited for an ultrasound scan. At the clinic, all inclusion/exclusion criteria will be assessed. All screening procedures will be documented in the appropriate study forms, including logs and case report forms. Clinical assessments and findings will also be documented as appropriate. No identifying information will be retained for women who do not enroll in the study.

First and enrollment visit – The first visit window for the ultrasound scan will be between 22–26 weeks of gestation. This window is selected because pregnancies at risk may be better identified and also visualization of fetal cardiac flow is possible. Based on the rigorous surveillance, we anticipate that most women will be in this window. The following information will be collected:

• Socio-demographic information such as women’s age, educational status, occupation• Medical history, including exposure to tobacco, gravidity, parity, past obstetric history (including number of miscarriages, stillbirths or neonatal deaths) and comorbid conditions (pre-eclampsia, diabetes mellitus)• Maternal anthropometry (height, weight and mid-upper arm circumference)• Maternal blood pressure• Haemoglobin of the mother (using Hemocue) (Hemocue Pholometer Model 301; Ängelholm, Sweden)• Symphysiofundal height will be measured• Four chamber view of the mother’s heart• Standard obstetric Doppler evaluation including the four primary ultrasound measures of fetal growth—head circumference, biparietal diameter, abdominal circumference, and femur length is routinely performed for all pregnant women presenting at the center. These parameters will be used to estimate fetal weight (automatically calculated by the machine).• Focused Fetal Doppler Echocardiography using Vivid iq Premium machine (GE Healthcare, Chicago IL, USA) and a curvilinear probe – These would include transabdominal measurements of the Doppler velocity of the umbilical artery obtained in the free loop of the umbilical cord, the middle cerebral artery (MCA) will be obtained in the proximal third of the vessel
^19^, close to its origin in the internal carotid artery in an axial section of the fetal brain. The ductus arteriosus and fetal aortic isthmus (AoI) flow velocities will be obtained either in a sagittal view of the fetal thorax with a clear visualization of the aortic arch or in a cross section of the fetal thorax at the level of the 3-vessel and trachea view, and measurements of left and right ventricular outflow will be imaged in an apical or basal 5-chamber view of the heart
^20^.

Second visit – The second visit window of ultrasound scan will be between 30–34 weeks of gestation. This will be applicable for all women who have had their first scan during 22–26 weeks of gestation as well as newly enrolled women during 30–34 weeks of gestational age. We have identified this window based on the antenatal care seeking in this setting, where the first point of contact of the pregnant woman with the health system is in the third trimester. The same procedures as described in the first visit will be done. However, at the second visit, cardiotocography (CTG) and umbilical artery continuous wave Doppler image through UmbiFlow device will also be obtained. All scans of a woman (whether 1 or 2) will be included in the model at the relevant gestational age time points. 

Follow up – We will obtain contact information (phone number) from all enrolled women. A trained research midwife will be responsible for making phone calls, as well as performing household visits for immediate and early identification of the pregnancy outcome. A hotline number and emergency transfer for delivery will be provided to the enrolled women. In case of live births, a team of CHWs will perform home visits to the baby at post-natal day 1 and 6. At the first visit, labor and delivery information including questions related to delayed cry, meconium passage and hospital course (if any) will be collected and the weight and length of the baby will be recorded. In subsequent visits, the baby will be examined by CHW for questions related to early neonatal sepsis on standardized questionnaires. Facilitated referral will be provided in case the mother or newborn requires treatment. In case of a stillbirth, the same labor and delivery information will be collected at day of outcome.

Please refer to
Figure 1 for the study flow diagram.

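### Scans from 22 weeks are used for prediction, but a fetal death delivered before 28 weeks is not a primary event, while a live birth at the same gestation that dies within 7 days is

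*Protocol article*

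**What the plan says.** All places are in the Protocol article, under Study protocol.

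- **Eligibility:** "Pregnant woman coming to the ultrasound clinic between 22–34 weeks of gestation".
- **First and enrollment visit:** "The first visit window for the ultrasound scan will be between 22–26 weeks of gestation". On uptake: "Based on the rigorous surveillance, we anticipate that most women will be in this window".
- **Second visit:** the 30–34 week window serves women already scanned once, "as well as newly enrolled women during 30–34 weeks of gestational age". Every scan, whether a woman has one or two, goes into the model at its gestational age. UmbiFlow is recorded only at this visit.
- **Outcomes, primary:** there are two. One reads "Stillbirth (baby born with no signs of life at or after 28 weeks of gestation", which sets a lower gestational limit. The other has no such limit: "Early neonatal mortality (death of a baby within the first 7 days of life".
- **Outcomes, secondary:** these include "Prematurity – Birth of a fetus < 37 weeks of gestation" and birth weight under 2.5 kg. Neither is restricted to live births. Miscarriage or fetal loss before 28 weeks is not listed.
- **Follow up:** procedures are given for a live birth and for a stillbirth, and for no other ending.
- **Statistical analysis and Data transfer and analysis:** women with and without an adverse perinatal outcome are compared, Doppler and model parameters are related to that outcome by logistic regression, and phenogroups are linked to outcome after unsupervised learning.

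**The concern.** The study asks whether fetal haemodynamics seen on a scan predict the death of that fetus or newborn. For a scan at 22–26 weeks, the period at risk begins at the scan. The primary outcomes leave a hole in the first part of that period: between the early scan and 28 weeks, a death counts only if the baby was born alive.

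These are the deaths closest in time to a scan that the plan placed early in order to find pregnancies at risk. If such a death is scored as no event, a fetus with abnormal Dopplers that then died looks like a false alarm, and one with normal Dopplers that then died looks like a correct reassurance. If the woman is dropped, the early scan is judged on a cohort from which its nearest failures and successes have been removed. The direction of the net distortion cannot be told in advance. With 25–30 events planned, a handful of deaths is enough to matter.

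**Working it through.** **1. The definitions applied to four pregnancies, each scanned at 23 weeks**

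| Course | Stillbirth outcome | Early neonatal death outcome | Primary event? |
|---|---|---|---|
| Dies in utero, delivered at 26 weeks | No (born before 28) | No (not born alive) | No |
| Born alive at 26 weeks, dies on day 1 | No | Yes | Yes |
| Dies in utero at 27 weeks, delivered at 28 weeks | Yes (birth is at 28) | No | Yes |
| Dies in utero and delivered at 32 weeks | Yes | No | Yes |

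Only the first row falls through. It differs from the second only in signs of life at birth. The third row matters because the definition turns on gestation at birth, not at death.

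**2. The plan's own event count**

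Inputs (Sample size estimation): 500 women, and "In the study area there are 30 stillbirths per 1000 total births while there are 30 neonatal deaths per 1000 live births".

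- Stillbirths: 500 × 30/1000 = 15.0
- Neonatal deaths: (500 − 15) × 30/1000 = 14.55
- Total: 29.55, inside the stated 25–30.

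This treats all neonatal deaths as falling in the first 7 days. The lower end of 25 corresponds to about 69% doing so (15 + 0.69 × 14.55 = 25.04); that share is not in the document.

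**3. Size of the gap**

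The document gives neither the rate of fetal death delivered between the early scan and 28 weeks nor the share of women scanned early (it says only most). Assumed ranges: rate r = 2–8 per 1000; share scanned early s = 50–100%.

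Unclassified deaths: x = 500 × s × r/1000. Share of all deaths: x/(29.55 + x).

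| s | r per 1000 | x | Share of all deaths |
|---|---|---|---|
| 50% | 2 | 0.5 | 0.5/30.05 = 1.7% |
| 50% | 8 | 2.0 | 2/31.55 = 6.3% |
| 100% | 2 | 1.0 | 1/30.55 = 3.3% |
| 100% | 8 | 4.0 | 4/33.55 = 11.9% |

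The range is therefore about 0.5–4 deaths, or roughly 2–12%. With the planned minimum of 25 events as the base, the ends become 0.5/25.5 = 2.0% and 4/29 = 13.8%.

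**4. Which analyses are exposed**

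- Group comparison, logistic regression and the step linking phenogroups to outcome: exposed, because each uses the outcome label.
- Unsupervised learning step: not exposed, because it uses no outcome label.
- UmbiFlow against the model: not exposed. UmbiFlow is recorded at 30–34 weeks, and a pregnancy that ended before 28 weeks has no reading.

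**The case against.** Several points against the concern are sound and limit it.

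- **The 28-week limit is a conventional definition.** It is not an error as a definition of stillbirth. The fault is only its mismatch with prediction from 22 weeks.
- **A reader might infer that every fetal death before 28 weeks is lost.** It is not: a death before 28 weeks that is delivered at or after 28 weeks counts.
- **A reader might infer that the sensitivity and specificity comparison is biased.** The only one stated is UmbiFlow against the model, and these pregnancies cannot enter it.
- **A reader might infer that the model would be trained on wrong labels.** Learning is unsupervised and the training data are mainly synthetic. Labels enter afterwards and could be reassigned then.
- **The losses might be caught elsewhere.** The article does not confine adverse perinatal outcome to the two primary outcomes, and prematurity and low birth weight are worded so that a fetal loss could fit. This stands in part: such a death would then be recorded, but among surviving preterm babies and not as a primary event. That it would otherwise be a non-event or be dropped is an inference from the absence of any rule.
- **The detail may be in a fuller document.** Handling of unusual endings can be left to one. The article, however, itself fixes the primary definitions, the scan windows and the use of early scans, and the gap follows from those.
- **A reader might infer survivor bias from women found at 27–29 weeks.** They are eligible but have no scan window until 30 weeks. Having to reach a scan is ordinary cohort entry, and no bias is shown. This is a mismatch of wording.

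**Conclusion.** The concern holds in a limited form. Among pregnancies scanned at 22–26 weeks, a fetal death delivered before 28 weeks is outside both primary outcomes, whereas a live birth at the same gestation followed by death within 7 days is inside. This follows from the text alone and needs no assumed figure. It affects the outcome-linked analyses of the early scan; women first enrolled at 30–34 weeks are untouched.

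The size cannot be fixed from the document. The 0.5–4 deaths rest on the assumed rate and early-scan share, and the 2–12% also on the plan's own event rates. A larger figure, 6–21% of fetal deaths, results if all 500 women are taken as scanned early and only the 15 stillbirths form the base: 1/16 to 4/19. The article does not support that as the headline, since it expects most rather than all women in the early window and its primary events include neonatal deaths.

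The point concerns the primary outcome, so it should be settled before outcome data are analysed.

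**What to change.** 1. For the prediction analyses, define the event as any fetal death after the index scan (from 22 weeks) or death within 7 days of birth. The index scan is the scan whose predictive value is being assessed, so a woman with two scans is counted from each in turn.
2. Keep stillbirth at or after 28 weeks as a separately reported rate, for comparison with the area figure.
3. Add a branch to Follow up for pregnancy loss before 28 weeks, recording gestation at delivery and signs of life.
4. Separately, reconcile the 22–34 week range under eligibility and Recruitment with the 22–26 and 30–34 week scan windows, so that it is clear how women found between the windows are handled.

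The cost is mainly wording plus one follow-up branch, because calls and home visits already follow enrolled women to the end of pregnancy. The small downside is that the composite departs from the conventional perinatal definition; item 2 covers that.

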## Discussion

The study will start recruitment in March 2018. Training the machine learning algorithms with data generated from the computational model and validating it in a population at risk would enable to identify the fetus and placenta that maybe compromised and be at risk for higher perinatal morbidity and mortality. This data would allow screening of pregnant women to detect at- risk and high-risk pregnancies. Early detection of these pregnancies would allow for timely referral to improve outcomes. Please refer to
Figure 3 for the clinical decision making algorithm that may be proposed.

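### Labour characteristics are named as inputs to the detection model, but they are known only at or after delivery and so cannot serve antenatal prediction

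*Protocol article*

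**What the plan says.** Under *Sample size estimation* (Study protocol), the article supports the adequacy of about 500 women partly by pointing to additional data: "we will be using socio-demographic, and pregnancy and labor characteristics, along with the Doppler", "where the combined analysis should make the detection additionally more robust".

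Under *Follow up*, it says when labour data are obtained. For live births, "a team of CHWs will perform home visits to the baby at post-natal day 1 and 6", and "At the first visit, labor and delivery information including questions related to delayed cry, meconium passage and hospital course (if any) will be collected". For the other case, "In case of a stillbirth, the same labor and delivery information will be collected at day of outcome".

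Under *Outcomes*, one secondary outcome reads "Birth asphyxia – Delayed cry after at least 1 minute of life".

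The intended use is antenatal. The end of the Introduction sets the aim of identifying fetuses at increased risk and of comparing the model's sensitivity and specificity with UmbiFlow's. The Discussion foresees screening of pregnant women and says "Early detection of these pregnancies would allow for timely referral to improve outcomes". Under *Data transfer and analysis*, a new individual is to be predicted by projecting her input data into the space learned by unsupervised Multiple Kernel Learning (MKL).

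**The concern.** A prediction model can use only what is known when the prediction is made. Here that moment is a scan at 22–26 or 30–34 weeks. Labour has not happened by then, so a model that needs labour inputs cannot be run on the woman it is meant to help.

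Two results are at stake. The first is the reported sensitivity and specificity: items recorded during or after delivery are closer to the outcome than any antenatal measurement, and can make the model look better than it would be in use. The second is the comparison with UmbiFlow, which has only an antenatal umbilical artery waveform. A model that also held intrapartum or postnatal information would start with an advantage that has nothing to do with the haemodynamic approach under test.

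**Working it through.** **1. The plan's own figures, for context.** The paragraph gives 30 stillbirths per 1000 births and 30 neonatal deaths per 1000 live births.
- Stillbirths: 500 × 0.030 = 15.
- Neonatal deaths: (500 − 15) × 0.030 = 14.55.
- Total: 29.55, within the stated 25–30.
- Enrolment: 500 × 1.05 = 525, as stated.

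These reproduce, and the point does not depend on them.

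**2. When each kind of input exists.**

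| Data | Where described | When known |
|---|---|---|
| Doppler, socio-demographics, history, anthropometry, blood pressure, haemoglobin | First and enrollment visit; repeated at Second visit | 22–26 and/or 30–34 weeks |
| CTG, UmbiFlow | Second visit | 30–34 weeks |
| Labour and delivery items, live birth | Follow up | Postnatal day 1 |
| Labour and delivery items, stillbirth | Follow up | Day of outcome |

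No labour item appears in the lists for the two antenatal visits. No sentence limits the model's inputs to what is known at the scan.

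**3. Overlap with the outcomes.**
- *Birth asphyxia (secondary):* defined by delayed cry, which is also one of the listed labour and delivery items. If that item is an input, predictor and outcome are the same.
- *Stillbirth and early neonatal death (primary):* no labour item defines either. The difficulty is that the information arises only at or after delivery, and for a stillbirth is collected when the outcome is already known.
- *Low birth weight (secondary):* weight is recorded at the same visit but is listed apart from the labour and delivery questions, so I do not count it.

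**4. Does unsupervised learning remove the problem?** No. It withholds the outcome labels, not the inputs. Labour variables would still help to shape the low-dimensional space and the phenogroups, which are afterwards related to outcome. A pregnant woman could not be projected on inputs she does not yet have.

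**5. Size: hypothetical illustrations only.** None of the AUCs or delayed-cry rates below is in the document.

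- *Adding a post-birth item.* Assume independent binormal predictors, with AUC *a* from antenatal data and *b* from the post-birth item. The combined AUC is Φ(√(z(a)² + z(b)²)), where z is the standard normal quantile. With *a* = 0.65 and *b* = 0.70: Φ(√(0.385² + 0.524²)) = Φ(0.651) = 0.74. With *a* = 0.75 and *b* = 0.90: Φ(√(0.674² + 1.282²)) = Φ(1.448) = 0.93. None of the gain over *a* is available at the scan.
- *Delayed cry alone, early neonatal death.* For one binary marker, AUC = (sensitivity + specificity)/2. Assume delayed cry in 40–80% of early neonatal deaths and in 3–10% of survivors. The range is (0.40 + 0.90)/2 = 0.65 to (0.80 + 0.97)/2 = 0.885.

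**The case against.** The strongest reply is that the point turns on one word in a sample size paragraph, which is not the model specification. The Abstract and Introduction describe a model based on Doppler patterns. The extra data listed in the Abstract are socio-demographics, anthropometry, haemoglobin and CTG. *Second visit* places scans in the model at their gestational ages. *Data transfer and analysis* names no labour variable, and its step of relating clusters to clinical findings could use labour data purely as description. Training data are to come mainly from a simulated fetal circulation, and nothing suggests that this simulation produces labour variables. The study is also a pilot, with validation in a larger population to follow.

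Much of this stands as a limit on the claim. The article does not say which labour items would enter, so a reader should not infer that delayed cry certainly will. It does not answer the point, because the sentence gives labour characteristics a stated task, improving detection alongside Doppler, and no other sentence withdraws it. This is a stated choice that conflicts with the stated use, not a detail left to a fuller document.

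Two stronger readings are tempting and are not supported:

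- *That the predictors partly define the primary outcomes.* Delayed cry defines birth asphyxia only.
- *That delayed cry alone would give an AUC of about 0.82–0.94 for the combined primary outcome.* The arithmetic is right: sensitivity (15 + 0.4 × 11.6)/26.6 = 0.738 with specificity 0.90 gives 0.819, and (15 + 0.8 × 10.2)/25.2 = 0.919 with 0.97 gives 0.945. But it assumes the share of neonatal deaths that are early and the delayed-cry rates. It also codes all 15 stillbirths as marker-positive, although the document does not say how the item applies to a stillbirth. That coding builds the outcome into the marker. It also treats one item as a stand-alone classifier, whereas its weight within MKL is unknown.

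**Conclusion.** The point holds in this form. As written, the plan adds to the detection model a class of data that the protocol collects only after birth or on the day of a stillbirth. Such data cannot be inputs to a model run at the 22–26 or 30–34 week scan. If they were used, apparent sensitivity and specificity, and any advantage over UmbiFlow, could be inflated and would not represent antenatal prediction. For birth asphyxia there would be circularity if delayed cry were included. For stillbirth and early neonatal death the defect is timing.

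The amount of inflation cannot be derived from the document, and the illustrative AUCs are not estimates for this study. The conclusion rests on two readings: that the sentence in the sample size paragraph means what it says about detection, and that the labour data it refers to are those described under *Follow up*, the only ones in the article.

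**What to change.** Delete labour from the inputs named under *Sample size estimation*, and add one sentence to the protocol or SAP. It should say that every input used for prediction (MKL, projection of new women onto phenogroups, any logistic prediction score) is restricted to variables measured at or before the index scan. Examples are Doppler and model-derived parameters, socio-demographics, history, anthropometry, blood pressure and haemoglobin, with CTG only when the index scan is the second visit.

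Labour and delivery data should be used only to describe phenogroups or aetiology after the model has been fixed.

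The change needs no new data and leaves the sample size and expected events as they are. Its one drawback is that apparent accuracy may be lower, because it will then reflect only what is known at the scan.
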